## Methods/design

### Study design and settings

The study will be a randomized, controlled, multicenter trial conducted at 4 medical centers, selected by the coordination center. The coordinating center comprise clinical experts, statisticians, and quality control experts, who will be responsible for clinical research methodology and resolving the key issues in the progress of research implementation. And they also have the responsibilities, including the design of the clinical research trial, selection of the cooperative hospitals, and provision of training courses including instructions manuals. The medical centers enrolled in this study are the Huangshi Hospital of Traditional Chinese Medicine, Tongji Hospital Tongji Medical College Huazhong University of Science and Technology, LaoHeKou Tradiational Chinese Medicine Hospital, and Leishenshan Hospital of Wuhan. A total of 160 patients that meet the eligibility criteria will be randomized into two groups (treatment group and control group) at a ratio of 1:1. The study flowchart is illustrated in Fig. 1. The Standard Protocol Items Recommendations for Interventional Trials (SPIRIT) checklist is presented in Additional file 1.

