### Sample size

A previous study [26] on COVID-19 by traditional Chinese medicine showed that the clinical cure rate in the conventional treatment group was 61.11%, while it was 91.18% in the group receiving traditional Chinese medicine plus routine treatment. According to the literature, presuming that the rate of the clinical effective rate in the treatment group is improved from 61.11 to 91.18%, the sample size is calculated according to the parameters *α* = 0.05 (two-sided test) and *β* = 0.1. Comparing the rates of the two groups with respect to the sample size estimation formula, we calculated that 41 patients should be recruited in each group. Studies with a similar patient population have the drop-out rate of 10% [27], and we will enroll a total sample size of 160 participants. We used the calculation tool on https://www.cnstat.org/samplesize/.

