### Randomization, allocation concealment, and blinding

The randomization sequence is generated by SPSS 19.0, using permuted small blocks of random size, stratified by medical center, and grouping the Chinese medicine group and the control group on a 1:1 schedule. The two sets of allocation codes are kept in opaque envelopes; one set is kept by the research sponsor and the other set by the pharmacy administrators, who then assign the study drug to the nurses for administration. This is an open-label study. The allocation concealment is blinded before the envelop is opened. After randomization, subjects randomized to the intervention arm will be receiving combined Shenhuang granule and Western medicine therapy, or only Western medicine therapy. The evaluators and statistician will be blinded until the completion of the visit and analysis. The statistical analysis is carried out by the professors of statistics at the Shanghai University of Traditional Chinese Medicine.

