### Outcomes and measurements

The primary outcome is clinical improvement up to 14 days after treatment. The definition of clinical improvement is that the patient’s admission status drops by 1 point on the 6-point scale or is discharged from the hospital, whichever comes first. The 6-point ordinal scale based on the well-defined WHO severity scale is as follows: 6 = death; 5 = critical, meet any of the following conditions: (1) respiratory failure, mechanical ventilation is required, (2) shock, (3) with other organ failure which requires ICU care; 4 = severe, meet any of the following criteria: (1) respiratory distress (≥ 30 breaths/ min), (2) oxygen saturation at rest ≤ 93%, and (3) arterial partial pressure of oxygen (PaO_2_)/fraction of inspired oxygen (FiO_2_) ≦ 300 mmHg; 3 = moderate, fever and respiratory symptoms, accompanied by radiological findings of pneumonia; 2 = mild, mild clinical symptoms, and no imaging signs of pneumonia; and 1 = discharged alive, (1) body temperature returned to normal for more than 3 days, (2) respiratory symptoms improved markedly, (3) pulmonary imaging showed obvious absorption of inflammation, and (4) the nucleic acid test of respiratory tract specimen is negative for 2 consecutive times.

Secondary outcomes are the mortality and rate of receiving invasive ventilator in the severe category, the improvement of oxygen saturation, and Acute Physiology and Chronic Health Evaluation (APACHE-II) score.

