### Statistical analysis

No interim analysis or subgroup analyses are planned for this trial. Full analysis set (FAS), per-protocol set (PPS), and safety analysis set (SS) will be conducted. FAS refers to the ideal set of eliminating of all subjects in a minimum and reasonable manner, according to the principle of intention-to-treat (ITT). PPS is a subset of ITT’s dataset, which has completed relevant observation according to the program requirements. The compliance of these subjects ranges from 80 to 120%, in which the subjects do not seriously violate the research program, complete all visits and CRF filling, and do not miss the main evaluation indexes and most other evaluation indexes. SS refers to all subjects who receive at least one treatment after randomization. All safety information records of subjects will be evaluated, including adverse events, severe adverse events, and clinically significant changes in safety indicators. The statistical analysis is performed in a blinded manner using the SPSS 20.0 software. For the continuous variables, the chi-squared test or Fisher’s exact test is used to compare the clinical improvement, oxygen saturation, and Acute Physiology and Chronic Health Evaluation (APACHE-II) score. Relative risk, risk difference, and number of treatments are reported with a 95% confidence interval. For the two categorical variables, we make comparison between groups and calculate the 95% CI using chi-squared tests. For the repeated measures data, category variance outcomes are analyzed using generalized estimating equations, and conclusions are drawn according to the estimating of parameter and standard error.

Our approach is to use the final observation status when no mortality is observed for 14 days, to ensure that we do not lose data about the primary outcome and the key secondary outcome. A *P* value < 0.05 is considered as statistically significant.

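### Randomisation is stratified by centre but the tests named for the primary outcome carry no centre term; if centres differ, the analysis is conservative and less precise than it could be

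*Protocol article*

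**What the plan says.** Study design and settings describes a "multicenter trial conducted at 4 medical centers, selected by the coordination center", in which 160 patients "will be randomized into two groups (treatment group and control group) at a ratio of 1:1". Under Randomization, allocation concealment, and blinding, the sequence is generated "using permuted small blocks of random size, stratified by medical center".

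The outcome is binary at the patient level: "The primary outcome is clinical improvement up to 14 days after treatment". In Statistical analysis, the sentence that names this outcome says that "the chi-squared test or Fisher’s exact test is used to compare the clinical improvement, oxygen saturation" and the APACHE-II score. Two further sentences follow: "Relative risk, risk difference, and number of treatments are reported with a 95% confidence interval" and "For the two categorical variables, we make comparison between groups and calculate the 95% CI using chi-squared tests". Generalised estimating equations are named for repeated measures only. Centre appears in none of these sentences, whether as a stratum or as a covariate.

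The Sample size section fixes the planned effect, "presuming that the rate of the clinical effective rate in the treatment group is improved from 61.11 to 91.18"%, with two-sided α = 0.05, β = 0.1, 41 patients per group before drop-out, 10% drop-out and a total of 160.

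**The concern.** Blocking within centre forces the arms to be nearly balanced at each hospital. Differences in outcome between hospitals then contribute almost nothing to the sampling variance of the arm difference. A pooled two-by-two test still estimates its standard error from the overall response rate, which includes those differences. If they exist, the standard error is too large, the p-value too high and the interval too wide. Fisher's exact test, the named alternative, ignores centre in the same way.

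What is at stake is precision and, possibly, some power. There is no risk of excess false-positive findings.

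**Working it through.** **1. The plan's own figure.** With p₁ = 0.6111, p₂ = 0.9118 and mean p̄ = 0.76145, the usual formula without continuity correction is

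n = [1.960·√(2p̄(1−p̄)) + 1.282·√(p₁(1−p₁) + p₂(1−p₂))]² / (p₂−p₁)² = (1.1813 + 0.7228)² / 0.3007² = 40.1, rounded up to 41 per group.

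This matches the article. The same method gives power of 0.996 at 80 per arm and 0.992 at 72 per arm (160 less 10%).

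**2. Size of the excess variance.** The article gives no centre-specific rates, so these are assumptions. For four equal centres with control rates p_k and mean m, the pooled test uses variance m(1−m). Under centre-blocked allocation the relevant variance is the average of p_k(1−p_k). Let r be the second divided by the first. The pooled test's actual type I error is then about 2·[1 − Φ(1.96/√r)].

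| Assumed centre rates | m(1−m) | mean p_k(1−p_k) | r | approx. type I error |
|---|---|---|---|---|
| 49/57/65/72% | 0.2384 | 0.2310 | 0.969 | 4.6% |
| 38/55/70/82% | 0.2373 | 0.2102 | 0.886 | 3.7% |
| 29/52/75/89% | 0.2373 | 0.1852 | 0.780 | 2.7% |

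**3. Simulation.** N = 160, four centres, permuted blocks of 2, 4 or 6 within centre, and 8,000 null trials per scenario (Monte Carlo standard error √(0.05·0.95/8000) = 0.24 points). The pooled chi-squared test with a Wald interval for the risk difference was compared with the Cochran-Mantel-Haenszel (CMH) test and a Mantel-Haenszel-weighted risk difference. The smaller effect, 61.11% vs 82%, is an assumption.

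| Four centres of 40 | Type I error, pooled / CMH | CI width, pooled / stratified | Power 61.11 vs 91.18%, pooled / CMH | Power 61.11 vs 82%, pooled / CMH |
|---|---|---|---|---|
| identical centres | 4.9 / 4.9% | 0.300 / 0.294 | 99.7 / 99.7% | 85.8 / 85.5% |
| 49–72% | 4.5 / 4.9% | 0.300 / 0.290 | 99.9 / 99.9% | 85.6 / 85.8% |
| 38–82% | 3.6 / 4.8% | 0.300 / 0.277 | 99.9 / 99.9% | 86.0 / 88.0% |
| 29–89% | 2.9 / 5.6% | 0.301 / 0.260 | 99.9 / 99.9% | 85.8 / 89.8% |

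With unequal centres (70/50/25/15) and the same four steps of centre difference, pooled type I error was 4.6, 4.9, 3.9 and 3.4%. The loss of power at 82% was about 0 to 2 points.

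**4. Coverage.** Null coverage of the pooled nominal 95% interval ran from 94.7% to 96.8%, rising with the centre differences. The simple stratified Wald interval covered 93.7–94.4%, slightly too low, so a little of its narrower width is not a true gain. From r in step 2, the genuine width ratio at the largest spread is √0.780 = 0.883, that is 0.300 × 0.883 = 0.265 rather than 0.260.

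**5. A harsher setting.** With 18 evaluable patients per arm per centre (72 per arm) and control rates of 35/50/72/87%, type I error was 3.1% pooled and 5.0% CMH; at 30/40/80/90% it was about 2.2% and 5.0%. At an assumed odds ratio of 2.5, power was 58% vs 64% and 50% vs 61%. The planned effect corresponds to an odds ratio of (0.9118/0.0882)/(0.6111/0.3889) = 6.58. At that value power was 98.9% vs 99.2% and 98.5% vs 99.0%.

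**The case against.** The strongest reply is that the article is silent rather than wrong: it never says that centre will be ignored, and adjustment is often left to an analysis plan, which is not shown here. That lowers confidence that the final analysis will be unstratified. It does not remove the point, because the article itself names the primary test, and the test as named does not follow the randomisation.

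The second reply is that the consequence is small, and this largely stands. A reader might infer from the mismatch that the p-values are invalid or that the trial is underpowered. The documents support neither. Any error lies in the conservative direction, and at the planned effect the two tests are indistinguishable in practice. The losses of 6 to 11 points in step 5 need an odds ratio of 2.5, which is not in the article, together with control rates spanning 52 to 60 points among patients who meet the same severity criteria. The article names four hospitals but gives no evidence that their outcomes differ to that extent.

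A reader might also argue that baseline status must be in the primary analysis, because improvement is counted from admission status and the exclusion criteria do not rule out ventilated patients. On a literal reading both level 4 and level 5 patients could enter. However, the inclusion criteria are the same three as for level 4, no effect of adjustment has been quantified, and the question is mainly one of eligibility.

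Finally, "For the two categorical variables, we make comparison between groups and calculate the 95% CI using chi-squared tests" is the general sentence on categorical variables. The sentence that names clinical improvement is the one introduced as covering continuous variables. Neither mentions centre.

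**Conclusion.** The mismatch between stratified randomisation and the tests named is real; its consequence is conditional and modest. With no or modest centre differences, the pooled chi-squared test has type I error of about 4.5–5% and loses nothing material. With large assumed differences it falls to about 3–4% (about 2% in the most extreme case tried), and intervals are up to about 13% wider than necessary (1/0.883 = 1.13 at the 29–89% spread). Power at 61.11% vs 91.18% is 98.5% or more with either test. A loss of 2 to 4 points appeared at 61.11% vs 82% with large centre differences, and more only under the harsher assumptions.

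Confidence is high in the mismatch and its direction. It is low in the size, which rests on assumed centre rates, centre sizes and a smaller effect that the article does not give. This is a point of efficiency and precision, not a failure of validity.

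**What to change.** In Statistical analysis, make the primary comparison of clinical improvement a Cochran-Mantel-Haenszel test stratified by the four centres. Report the Mantel-Haenszel risk difference and relative risk with 95% confidence intervals, using a variance estimator suited to small strata, given the slight under-coverage of the simple Wald form. Analyse mortality and invasive ventilation in the same way where event counts allow. A logistic model with centre and baseline status may be added as an optional supporting analysis.

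The cost is a change of text, settled before any unblinded analysis. It needs no new data and no change to the sample size. In these simulations the stratified test kept its level (4.8–5.6%) and gave up essentially nothing when the centres were alike.

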### Patient withdrawal

The rejection and withdrawal criteria are as follows:
Adverse events and complications occur, and the investigator considers that it is necessary to terminate the trialVoluntary withdrawalThose who are lost follow-up

In patient withdrawal, all study interventions will cease. All data captured up to this point in time is stored in the database, and safety-related data are documented until day 14 if possible. Data from such patients become the dataset for efficacy and safety analysis on day 14.

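### The last-status rule, with only safety data sought after withdrawal, in effect counts unknown vital status as alive and fixes unimproved withdrawals as failures

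*Protocol article*

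**What the plan says.** Under Statistical analysis, the protocol article fixes one rule for incomplete outcomes: "Our approach is to use the final observation status when no mortality is observed for 14 days". The reason given is "to ensure that we do not lose data about the primary outcome and the key secondary outcome". The key secondary outcome is not named there.

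Under Patient withdrawal, patients may leave because of an adverse event or complication, by their own choice, or through loss to follow-up. For them, "All data captured up to this point in time is stored in the database, and safety-related data are documented until day 14 if possible". The section then adds: "Data from such patients become the dataset for efficacy and safety analysis on day 14".

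Under Outcomes and measurements, "The primary outcome is clinical improvement up to 14 days after treatment", where improvement means a one-point fall on the ordinal scale or discharge, whichever happens first. The list of other outcomes begins: "Secondary outcomes are the mortality and rate of receiving invasive ventilator in the severe category". None of them is labelled as key.

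Under Randomization, allocation concealment, and blinding: "This is an open-label study". Evaluators and statistician are to be blinded, but patients and treating staff are not.

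**The concern.** Read together, the two sections let the last status before withdrawal stand as the day-14 result, unless a death happens to be observed. Three consequences follow.

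- **Vital status.** If nobody learns whether a withdrawn or lost patient died, no death has been observed and the patient is in effect counted among the survivors.
- **Unimproved withdrawals.** Someone who leaves after an adverse event or complication without having improved is fixed as a failure. Efficacy status is not among the data said to continue after withdrawal, although it could often be obtained up to day 14.
- **Death after a brief improvement.** The improvement is correctly recorded, but a later death may go unseen.

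The patients have severe disease, and one withdrawal reason is clinical deterioration in all but name, so withdrawal can carry information about outcome. Treatment is open and only one arm takes the granule, so reasons and timing may differ between arms. What is at stake is the mortality comparison and, to a lesser degree, the primary comparison. The rule is meant to avoid losing data, but it fills gaps that follow-up could have closed.

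**Working it through.** **Inputs.** From Sample size: 160 patients, allocated 1:1 (80 per arm); drop-out 10%; rates 61.11% and 91.18%; two-sided alpha 0.05; beta 0.1. The article gives no mortality rate and no drop-out by arm, so both are assumed below and shown as ranges.

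**The plan's own figure.** With pooled variance and mean rate 0.76145:

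n = [1.960 × √(2 × 0.76145 × 0.23855) + 1.2816 × √(0.6111 × 0.3889 + 0.9118 × 0.0882)]² / 0.3007² = (1.181 + 0.723)² / 0.0904 = 40.1, rounded up to 41 per group.

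This matches the article. The point does not rest on it.

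**Patients exposed to the rule.** 10% of 80 = 8 per arm, 16 in all. This is an upper figure, because some of these patients will have a known outcome.

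**Mortality.** Each unobserved death lowers an arm's recorded mortality by 1/80 = 1.25 points. If 10% of patients have unknown vital status and all are counted as alive, recorded mortality is 0.9 × the completers' rate:

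| Assumed mortality in completers | Recorded | True, drop-outs at same rate | True, drop-outs at twice the rate |
|---|---|---|---|
| 10% | 9% | 10% | 11% |
| 20% | 18% | 20% | 22% |
| 30% | 27% | 30% | 33% |

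If the unknowns are unequal (assumed 5% in control, 15% in the granule arm) and true mortality is equal, the recorded risk ratio is 0.85/0.95 = 0.895. That is a difference of 1 to 3 points over the same mortality range. Swapping the two drop-out rates reverses the direction.

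**Primary outcome.** Take 72 patients per arm with known outcome and 8 per arm who left unimproved with unknown later status (Pearson chi-squared, no continuity correction).

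At the planned rates, 72 × 0.6111 ≈ 44 control and 72 × 0.9118 ≈ 66 granule patients improve:

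| Scoring of the 8 per arm | Control | Granule | Difference | p |
|---|---|---|---|---|
| All not improved | 44/80 | 66/80 | 27.5 points | 0.0002 |
| Worst case for granule | 52/80 | 66/80 | 17.5 points | 0.012 |
| Best case for granule | 44/80 | 74/80 | 37.5 points | < 0.0001 |

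With a smaller assumed effect, 44/72 versus 56/72 (p = 0.030 among those observed):

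| Scoring of the 8 per arm | Control | Granule | Difference | p |
|---|---|---|---|---|
| All not improved | 44/80 | 56/80 | 15 points | 0.050 |
| Worst case for granule | 52/80 | 56/80 | 5 points | 0.50 |
| Best case for granule | 44/80 | 64/80 | 25 points | 0.0007 |

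The first row of each table is what the last-status rule itself gives for patients who leave unimproved.

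**The case against.** The strongest reply concerns the primary outcome. A reader might infer that an improvement seen before withdrawal is wrongly frozen as a success. The documents do not support this: the endpoint is an event at any time up to day 14, so such a patient has already met it and nothing is imputed. Likewise, carrying forward a status of not improved equals ordinary non-responder scoring. Both points stand. What remains for the primary outcome is that an observable result is left uncollected.

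A reader might also infer that the plan expressly counts unknown patients as alive, and does so for mortality. Neither is written. Counting them as alive follows from making the rule depend on an observed death. Mortality as the key secondary outcome is an inference from its place at the head of the list and from the wording of the rule.

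Nor does every death after withdrawal disappear. Safety data continue where possible, serious adverse events are reported promptly, and Monitoring of compliance asks for contact after transfer or discharge. Only patients whose vital status is truly not obtained are affected.

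Finally, a reader might infer a bias in favour of the granule. The withdrawal criteria apply to both arms and no drop-out by arm is given, so a difference is plausible but not shown. Multiple imputation and similar detail may sit in a full protocol or analysis plan that is not shown; its absence here is no fault.

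The rule could be meant only for patients known to be alive at day 14. Its stated purpose of not losing outcome data, and the inclusion of withdrawn and lost patients in the efficacy analysis, make that reading hard to sustain.

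**Conclusion.** The point holds in limited form. As written, the plan can count patients of unknown vital status as survivors, and it leaves efficacy status after withdrawal uncollected while still using those patients at day 14.

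At most about 8 patients per arm are affected at the planned drop-out. If all of them had unknown vital status and died at the same rate as the others, recorded mortality would be nine tenths of the true rate, and lower still relative to the truth if they died more often. These mortality figures rest on assumed rates, and they matter for a named outcome only if mortality is the key secondary one. The direction of any difference between arms cannot be stated.

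For the primary outcome, the conclusion at the planned 61% versus 91% is robust to worst-case scoring. It would be fragile only if the true effect were much smaller, as in the 44/72 versus 56/72 illustration.

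**What to change.** 1. In Patient withdrawal, state that stopping the granule or leaving treatment does not end follow-up. Record the 6-point score and vital status to day 14 for every randomised patient who has not withdrawn consent to data use, by chart or telephone. Monitoring of compliance already foresees contact after transfer or discharge. This changes data collection only, not when treatment stops.
2. In Statistical analysis, replace the last-status rule. Keep any improvement observed by day 14 as an event, in line with Outcomes and measurements. Score patients with no observed improvement and unknown later status as not improved in both arms. Treat unknown vital status as missing, not as alive.
3. Name the key secondary outcome.
4. Report a best- and worst-case sensitivity analysis. It is needed because scoring as not improved is itself a single imputation.

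The cost is revised wording in two sections, contact with up to about 16 patients, and possibly slightly less favourable rates. For patients enrolled before the change, day-14 status can be sought from the chart.
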